**Table 1. Evaluation Schedule of Assessments and Measures by Time Point**

|                                                                                    | 1wk (R) | 3wk (I) | 8wk (I/R) | 16wk (R) |
|------------------------------------------------------------------------------------|---------|---------|-----------|----------|
| Anthropometry                                                               |         |         |           |          |
| Anthropometry - Baby                                                               | X       | X       | X         | X        |
| Anthropometry - Mother                                                             |         | X       | X         | X        |
| Anthropometry - Father                                                             |         | X       | X         | X        |
| Sleep Outcomes                                                              |         |         |           |          |
| Parent report of infant sleep - Brief Infant Sleep Questionnaire (BISQ)            |         | X       | X         | X        |
| Parent report of own sleep – Insomnia Symptom Questionnaire (ISQ)                  | X       |         | X         | X        |
| Maternal Actigraphy                                                                |         |         | X         |          |
| Infant Actigraphy                                                                  |         |         | X         |          |
| Infant Soothe and Feeding                                                   |         |         |           |          |
| Infant soothing – Babies Need Soothing                                             |         |         | X         | X        |
| Infant temperament - Infant Behavior Questionnaire                                 |         |         |           | X        |
| Feeding frequency - Babies Need Feeding                                            |         | X       | X         | X        |
| Baby's eating behavior – Baby Eating Behavior Questionnaire (BEBQ)                 |         |         |           | X        |
| Parent Outcomes                                                             |         |         |           |          |
| Parenting self-efficacy - Karitane Parenting Confidence Scale                      |         |         | X         | X        |

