| Maternal feeding practices and beliefs – Infant Feeding Style Questionnaire (IFSQ) |         |         | X         | X        |
| Maternal depression – CES-D                                                        | X       |         | X         | X        |
| Self-reported physical health                                                      |         |         |           | X        |

|                                                                         |   |   |   |   |
|-------------------------------------------------------------------------|---|---|---|---|
| Child Safety Outcomes                                                   |   |   |   |   |
| Safe sleep practices – Fowler                                           | X |   |   | X |
| Child safety practices – Framingham Safety Survey                       |   |   |   | X |
| Stress-Support Moderators                                               |   |   |   |   |
| Maternal Personality – Mini IPIP                                        | X |   |   |   |
| Family Background – Risky Families Questionnaire                        | X |   |   |   |
| Financial strain/employment – Assorted questions                        | X |   |   |   |
| Discrimination – Schedule of Racist Events                              | X |   |   |   |
| Romantic relationship characteristics – Assorted questions              | X |   | X | X |
| Co-parent relationship characteristics – Coparenting relationship scale |   |   |   | X |
| Social support – Social Provisions Scale                                | X |   |   |   |
| Family routines - Confusion, Hubbub and Order Scale (CHAOS)             |   |   | X |   |
| Demographics and Health History                                         |   |   |   |   |
| Family demographics, maternal/infant health                             | X |   |   |   |
| Intervention-Related Variables                                          |   |   |   |   |
| Co-parent involvement in intervention                                   |   | X | X |   |
| Implementation quality                                                  |   | X | X |   |

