### Intervention-Related Variables

*Coparent involvement in intervention.* While paternal and/or coparent involvement in the study is not required for participation, fathers and/or coparents will be strongly encouraged to attend study visits so they too can receive the study intervention. We will collect data on their attendance and degree of participation in the intervention visits.

*Implementation quality.* Our previous evaluations gave us the opportunity to evaluate participants' responses to training and evaluation materials and this has led to revised and simplified training and assessment tools, suitable for those reading at a 6th grade level. As in our previous studies, we also include measures immediately after study visits to systematically assess the quality of intervention staff's implementation of the intervention. These measures will be completed by the Community Research Associates (CRAs) delivering the intervention (see below). These data will provide information on overall implementation quality in our sample and will also allow implementation quality to be investigated as moderator of intervention effects. We will use parallel measures with the child safety control group to assess implementation quality.

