## **7. Data and Specimen Management**

a. Describe the data analysis plan, including any statistical procedures:

☐  
N/A

Data analysis will be led by [name], who has expertise in the analysis of longitudinal data. [name]., Assistant Research Scientist and Statistician at CFR, will provide statistical support for the conduct of analyses. All primary statistical analyses will invoke the intent-to-treat paradigm, analyzing data based on randomized assignment. Missing data will be handled using full-information maximum likelihood methods, which use all available information to estimate parameters, making this approach more efficient and less biased than other methods when data are missing at random. All models considered allow for the inclusion of relevant covariates. Covariates to be considered in refining the analyses, in addition to those described in detail in the proposed analyses below, include demographic factors (e.g., maternal employment and hours worked, gestational diabetes), weight-related factors (e.g., maternal pre- pregnancy weight/BMI, gestational weight gain, maternal smoking), and intervention-related factors (e.g., implementation quality, coparent involvement in intervention). We will also examine (1) infant sex as a covariate, given different growth charts for boys and girls and (2) feeding mode as a covariate, given differences in weight gain between breastfed and formula-fed infants.

**Specific Aim 1: The Effects of Sleep SAAF on Infant Weight and Rapid Weight Gain.** In Specific Aim 1 the primary outcomes are infant weight and changes in weight. BMI is generally assumed to be the standard growth measure for assessing obesity-risk in children age 2 years and older, but there is not one universally accepted measure for children younger than age 2 years. Recent data suggests that infant BMI at age 2 months is more strongly associated with obesity at age 2 years than is weight-for-length. Accordingly, BMI z scores will be our primary outcome, but we will also consider models that examine a range of other weight outcomes, including weight for length z-scores, percentiles, and weight for age z-scores; we anticipate that change across different indices of weight gain will be highly correlated and lead to similar conclusions in tests of program impact as well as tests of potential moderators and the hypothesized mediational model.

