| 
age z-score > +0.67, as described by Ong and Loos. This increase corresponds to crossing adjacent major centile lines on the standard CDC growth charts. The analysis for these rapid weight gain scores will be a repeated measures analysis, assessing the intervention effects on rapid weight gain scores from age 3 weeks up to age 16 weeks. The analysis will use generalized estimating equations (GEE) with a logit link, an extension of logistic regression which allows for repeated measurements on binary data, and will include infant weight adjusted for gestational age as a covariate. Because it is unlikely that within an 16-week period we will have many infants who meet the criteria for rapid weight gain based on the upward percentile crossing approach, we will also calculate conditional weight gain scores (CWG) following the method of Griffiths and colleagues, as described in our recent work.
 
Specific Aim 2: The Effects of Sleep SAAF on Parental and Infant Behaviors that Mediate Effects on Infant Growth. In Specific Aim 2 the primary outcomes are parental behaviors (parental self-efficacy, sleep/soothing practices, feeding practices, family chaos) and infant behaviors (sleep, soothing, and feeding) targeted by the intervention that may mediate effects on infant growth. We examine these effects in several steps.
 
First, we will examine differences between the Sleep SAAF and control groups in these outcomes at two time points post-intervention (8- and 16- weeks postpartum) using the linear mixed-effects model described above. The linear mixed-effects model will include intervention group and infant weight adjusted for gestational age. These analyses will test whether the Sleep SAAF group and the control group differ in these behaviors post-intervention and will be used to identify variables for the formal test of mediation.
 
Second, we will examine whether parent and infant behaviors mediate infant weight outcomes. We will test these hypotheses using structural equation modeling (SEM). The first step in demonstrating mediation is to establish the effects on mediating and distal outcomes, as we described above. We then specify mediators as indirect effects in a path model. Intervention condition will be dummy coded and specified as a predictor of infant and parental behaviors, which in turn predict infant weight and weight gain. The significance of the mediating process will be tested using the Sobel or bootstrapping methods.
 
Specific Aim 3: Moderation of Intervention Effects by Individual and Contextual Factors. In Specific Aim 3 we consider whether individual (depressive symptoms) and contextual (socioeconomic stressors, race-based stressors, romantic relationship characteristics, coparent relationship characteristics, social support) factors at 1 week postpartum moderate program effects. These factors will be included in the analyses described above to determine whether they moderate intervention effects on weight outcomes (Specific Aim 1) and parental and infant behaviors (Specific Aim 2).
 
As an exploratory analysis, we will also evaluate whether the individual and relationship variables differ between the Sleep SAAF group and the control group at 16 weeks postpartum. Doing so will allow us to examine whether improving infant sleep and soothing has secondary benefits for mothers' individual and relationship functioning.
 |                                         |

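### The optional covariate list in section 7.a lets intent-to-treat models adjust for variables recorded after randomisation, which could bias the estimated effect of assignment

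*Supplement*

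**What the plan says.** All of this is in the latest version of the protocol in the Supplement.

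- **Estimand (7.a).** "All primary statistical analyses will invoke the intent-to-treat paradigm, analyzing data based on randomized assignment".
- **Covariate list (7.a).** It opens with "Covariates to be considered in refining the analyses, in addition to those described in detail in the proposed analyses below". It then names demographic factors, weight-related factors and "intervention-related factors (e.g., implementation quality, coparent involvement in intervention". It also proposes to examine infant sex and "feeding mode as a covariate, given differences in weight gain between breastfed and formula-fed infants".
- **Named models (7.a).** The 16-week model contains arm and 1-week weight adjusted for gestational age. The growth, GEE and Aim 2 models contain arm, infant weight adjusted for gestational age and, where relevant, time.
- **Other use of implementation quality (6.a, Intervention-Related Variables).** The ratings will also "allow implementation quality to be investigated as moderator of intervention effects".
- **Aim 2 (7.a).** The outcomes include "infant behaviors (sleep, soothing, and feeding) targeted by the intervention that may mediate effects on infant growth".

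No section limits the treatment-effect models to covariates measured before allocation.

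**The concern.** Randomisation makes the arms comparable on everything fixed before allocation. A covariate recorded afterwards may itself be changed by allocation. Conditioning on it then removes the part of the effect that runs through it. It can also link the arms to unmeasured family factors that influence both the covariate and infant weight. The arm coefficient from such a model is not the effect of assignment that 7.a claims to estimate.

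Implementation quality and coparent involvement are close to measures of treatment delivery and receipt. Staff rate implementation quality after delivering one of two different curricula, so a given score need not mean the same thing in both arms. Neither variable can be observed for a dyad that misses both intervention visits.

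The list is also optional, with no rule for keeping or dropping a covariate. The trial is not blinded (6.c) and 7.a considers several weight indices. The choice of adjustment set could therefore follow the results unless it is fixed beforehand.

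**Working it through.** **Step 1: timing.** Randomisation is the first listed step of Home Visit 1, at 7–10 days. Against that:

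| Variable | When recorded | Source | Status |
|---|---|---|---|
| Implementation quality | 3 and 8 weeks | Table 1; 6.a | After randomisation |
| Coparent involvement (row "Co-parent involvement in intervention") | 3 and 8 weeks | Table 1; 6.a | After randomisation |
| Feeding mode, by the scale said to measure it (row "Feeding frequency - Babies Need Feeding") | 3, 8 and 16 weeks | Table 1; 6.a, Infant Soothe and Feeding Outcomes | After randomisation if this scale is used |
| Feeding mode, as an infant covariate | Grouped with a block marked at 1 week | 6.a, Demographics and Health; Table 1 | Unclear |
| 1-week weight | Home Visit 1, listed after randomisation | Home Visit 1 list | Same visit; order matters |

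**Step 2: reach of the list.** The list is stated to be in addition to the covariates named for each model, so it can attach to the 16-week model. It is only to be considered, so that model as written does not contain it.

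**Step 3: size.** The plan gives neither the effect of allocation on these variables nor their effect on weight, so there is no plan figure to reproduce or correct. The following is an illustration under assumed values.

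Let M be the covariate, standardised within arm. Let allocation raise M by *a*. Let M lower weight with slope *b*. Let an unmeasured cause raise M and lower weight, each with loading *c*. In a linear model the coefficient on M is −(*b* + *c*²), so adjusting for M shifts the arm coefficient by

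shift = *a* × (*b* + *c*²).

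Take a true total effect of −0.34 SD, borrowing the plan's detectable effect (7.b) purely as a yardstick:

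| *a* | *b* | *c* | Shift | Adjusted estimate |
|---|---|---|---|---|
| 0 | any | any | 0 | −0.34 |
| 0.2 | 0.2 | 0 | 0.2 × 0.2 = 0.04 | −0.30 |
| 0.2 | 0.4 | 0.4 | 0.2 × (0.4 + 0.16) = 0.112 | −0.23 |
| 0.4 | 0 | 0 | 0 | −0.34 |
| 0.4 | 0.2 | 0 | 0.4 × 0.2 = 0.08 | −0.26 |
| 0.4 | 0.4 | 0.4 | 0.4 × (0.4 + 0.16) = 0.224 | −0.12 |

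A simulation with 1,000,000 records per scenario agrees: in the last row the shift was 0.222. Without M in the model the estimate stayed at about −0.34 throughout. The movement towards zero follows from the signs assumed here; other signs could move it away from zero.

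**The case against.** The strongest reply is that no model written out in 7.a contains any of the three variables. The 16-week analysis has only arm and 1-week weight. This stands. A reader might infer that the planned primary estimate is already biased, and the documents do not support that.

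Second, nothing in the documents shows that allocation affects implementation quality or coparent involvement. Fathers and coparents are encouraged to attend without reference to arm, the arms have equal numbers of visits, and parallel quality measures are used in the control arm. This also stands as a statement about evidence: with no effect of allocation on the covariate, the shift is zero. It does not make the adjustment safe, because the variables are recorded during delivery of the two programmes and their balance is not guaranteed by randomisation.

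Third, a reader might infer that feeding mode is plainly a mediator because Aim 2 covers feeding. The documents stop short of this. Section 1 hypothesises less feeding to soothe and fewer feedings, not a switch between breast milk and formula, and the curriculum in 6.b addresses parents using either. The time point is ambiguous as well. What remains is that the plan should fix it.

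Fourth, implementation quality has a separate planned use as a moderator. That is true, but 7.a also lists it as a covariate, so the moderator use does not remove the problem.

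**Conclusion.** The concern holds as a point about what the plan permits. Section 7.a claims intent-to-treat and, in the same paragraph, allows effect models to be refined with two variables that are certainly recorded after randomisation and a third whose timing is not fixed. If they are added and allocation affects them, the adjusted arm coefficient could be biased for the effect of assignment.

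The size cannot be derived from the documents. The range of 0 to about 0.22 SD above rests wholly on assumed inputs and includes zero. It would be wrong to quote any percentage of the detectable effect as the loss in this trial. The 16-week model as named is unaffected. The point should be settled before analysis because the correction is simple and the covariate set is otherwise open.

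**What to change.** In 7.a:

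1. Remove implementation quality and coparent involvement from the covariates for the Aim 1 and Aim 2 treatment-effect models.
2. Allow feeding mode only if it comes from a report made before allocation, and state the source and time point.
3. Limit these models to one prespecified set of baseline covariates that the plan already contains: 1-week weight adjusted for gestational age, infant sex, pre-pregnancy BMI and maternal smoking.
4. State that 1-week weight is measured before allocation is revealed at Home Visit 1, and reorder the listed steps of that visit to match.
5. Keep the post-randomisation variables for fidelity, process and mediation analyses, labelled as such.

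Feeding intention, named in section 1 as a possible moderator, has no specific item in Table 1. It should not be relied on as a substitute for feeding mode unless the team confirms that it was collected before allocation.

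The cost is a change of wording in 7.a and in the Home Visit 1 list, plus a check of the order actually followed at visits already done. No new measurements are needed.

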### Home Visit 1: (Home, 7-10 days postpartum, Community Research Associate (CRA))

1. Randomize and provide appropriate introductory materials (intervention or control) to mother-infant dyads
2. Complete questionnaire measures
3. Measure infant weight and length
4. Measure maternal weight
5. Measure paternal weight

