## Infant Growth

*Infant weight and length.* At each home visit, infant weight and recumbent length/height will be measured by research staff trained in obtaining anthropometrics, and will be used to calculate weight-for-length and BMI percentile and BMI Z-score based on percentiles for age and sex established by the WHO (for outcomes <2 years) and CDC (for outcomes 2 years and up). Weights will be obtained using Medela Baby Weigh II infant scales. Recumbent lengths will be obtained in triplicate with Seca Model 416 recumbent length board. Head circumference will be measured using Seca Model 212 band and mid-thigh circumference will be measured using a flexible anthropometric measuring tape.

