### Demographics and Health

*Family demographics and maternal/infant health.* Parent and demographic covariates will include: Pre-pregnancy BMI, smoking during pregnancy, gestational weight gain, maternal type 2 or gestational diabetes mellitus, maternal and paternal BMI assessed at the first research visit, income, education, and employment (work status, hours worked). Infant covariates will include: Infant weight at age 1 week (the first assessment) adjusted for gestational age, child sex, and feeding mode (predominantly breastfed if 80% or more of milk feedings were breastmilk, predominantly formula-fed if 80% or more of milk feedings with formula milk, or mixed-feedings).

*Parent weight and height.* Mothers' pre-pregnancy weight and weight prior to delivery will be obtained from chart abstraction, if available. Should these data be missing from charts, it will be collected via survey. Mother's height will be measured using stadiometer at AU and weight will be measured using a calibrated scale at AU. At all subsequent visits, mothers and fathers will again be weighed using calibrated scales.

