First, we will examine differences in BMI and other weight outcomes at 16 weeks between the Sleep SAAF group and the control group using a linear mixed-effects model. The linear mixed-effects model will include intervention group and infant weight at age 1 week adjusted for gestational age. These analyses will test whether the Sleep SAAF group and the control group differ in their weight outcomes at age 16 weeks, which has previously been linked to child obesity risk at age 2 years.

Next, we will consider growth models that examine rate of change in weight from birth to 16 weeks. We will conduct growth curve analyses using hierarchical linear modeling to test whether the Sleep SAAF and control groups differ in their rate of change in weight over time. The model will include intervention group, time of growth measure, and infant weight adjusted for gestational age. These analyses will evaluate whether the Sleep SAAF group shows less of an increase in weight over time compared to the safety control group.

As an additional test of rapid weight gain, weight gain z-scores will be calculated for each measurement subsequent to the first intervention session at age 3 weeks (8 weeks and 16 weeks). Rapid weight gain scores will be calculated as an increase in weight-for-

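### The primary 16-week BMI z model adjusts for 1-week weight but not for the infant's own 1-week BMI z, which is already collected; adding it is a free improvement

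*Supplement*

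**What the plan says.** All references are to the later protocol version in the Supplement.

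- **Outcome.** Section 7a, Specific Aim 1, states "Accordingly, BMI z scores will be our primary outcome". The power statement in 7b places it at 16 weeks. Weight-for-length z and weight-for-age z are among the further outcomes.
- **Model.** For the 16-week comparison the same section specifies a linear mixed-effects model with two terms: the treatment group and "infant weight at age 1 week adjusted for gestational age". No other term is specified.
- **Infant covariates.** Section 6, Demographics and Health, lists "Infant weight at age 1 week (the first assessment) adjusted for gestational age, child sex, and feeding mode". It does not list 1-week BMI z.
- **What is measured at 1 week.** The Home Visit 1 list includes "Measure infant weight and length", and Table 1 marks baby anthropometry at 1 week. Under Infant Growth, "At each home visit, infant weight and recumbent length/height will be measured by research staff trained in obtaining anthropometrics", with length taken in triplicate. These measures are used to calculate "weight-for-length and BMI percentile and BMI Z-score based on percentiles for age and sex established by the WHO".
- **Other covariates.** Section 7a lets further covariates be considered. It names demographic, maternal weight-related and intervention-related factors, infant sex and feeding mode.

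**The concern.** In a randomised comparison of a continuous outcome, the usual first choice of covariate is the baseline value of that outcome. Here the outcome combines weight and length, while the specified baseline term is weight. Two infants of equal weight and gestational age but different length at 1 week have different baseline BMI z, and the planned model treats them alike.

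Two things are at stake. The first is precision: any predictive information in 1-week BMI z beyond weight stays in the residual. The second is chance imbalance: if the arms happen to differ in 1-week BMI z at similar weight, the planned model removes only the part that weight carries. The same weight covariate serves the other indices too, so the point also applies to weight-for-length z. It matters little for weight-for-age z, whose baseline is close to weight itself.

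**Working it through.** **Inputs from the documents (section 7b).** Two-sided 5% test, 80% power, 175 per arm, 10% attrition, stated detectable d of 0.34. The calculation uses no covariate.

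**The plan's own figure.** Completers per arm: 175 × 0.9 = 157.5. A two-sample t-test (noncentral t) gives a detectable d of 0.317. The normal approximation agrees: (1.960 + 0.842) × √(2/157.5) = 0.316. The stated 0.34 is therefore not reproduced; it needs about 136 to 137 completers per arm. That is a separate matter, it errs on the cautious side, and it does not affect this point. I use 0.317 below.

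**Inputs assumed, because the documents give none.** Let r_w be the correlation of 1-week weight with 16-week BMI z, r_b the same for 1-week BMI z, and ρ the correlation between the two covariates. Take r_w = 0.2 to 0.3 and r_b = 0.3 to 0.5.

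**Step 1: the two covariates one at a time.** Residual variance is proportional to 1 − r², so the ratio of BMI z to weight is (1 − r_b²)/(1 − r_w²).

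| r_w | r_b | Ratio | Change in variance |
|---|---|---|---|
| 0.3 | 0.3 | 0.91/0.91 = 1.00 | none |
| 0.2 | 0.3 | 0.91/0.96 = 0.948 | 5% less |
| 0.3 | 0.5 | 0.75/0.91 = 0.824 | 18% less |
| 0.2 | 0.5 | 0.75/0.96 = 0.781 | 22% less |

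Outside the assumed range the order can reverse: r_w = 0.4 with r_b = 0.3 gives 0.91/0.84 = 1.083, or 8% more variance.

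**Step 2: detectable d** = 0.317 × √(1 − r²).

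- Weight: 0.310 (r = 0.2) to 0.302 (r = 0.3).
- BMI z: 0.302 (r = 0.3) to 0.274 (r = 0.5).

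**Step 3: adding BMI z and keeping weight.** R² = (r_w² + r_b² − 2 r_w r_b ρ)/(1 − ρ²). With r_w = 0.3, r_b = 0.4, ρ = 0.7:

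- R² = (0.09 + 0.16 − 0.168)/0.51 = 0.161.
- Ratio against weight alone: (1 − 0.161)/(1 − 0.09) = 0.922, about 8% less variance.
- Detectable d: 0.317 × √0.839 = 0.290, against 0.302 with weight alone.

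Written as a reduction, the gain is (r_b − ρ r_w)²/[(1 − ρ²)(1 − r_w²)]. This is never negative and is zero only when r_b = ρ r_w, that is, when BMI z adds nothing beyond weight. Even at r_w = 0.4, r_b = 0.3, ρ = 0.7, where a swap loses 8%, adding gives 0.02²/(0.51 × 0.84) = 0.001, essentially no change.

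**Step 4: chance imbalance.** In the Step 3 example the standardised slope on 1-week BMI z, given weight, is (0.4 − 0.7 × 0.3)/0.51 = 0.37. A chance difference between arms in 1-week BMI z at equal 1-week weight would thus carry into the 16-week comparison at about 0.37 SD per SD, and the planned model would not remove it.

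**The case against.** **Nothing shows that weight is the weaker predictor.** This stands. No correlation with 16-week BMI z is given for either measure. BMI divides by length squared, so it carries any error in measuring a newborn's length, which weight does not. A reader might infer that precision is certainly lost, or, by pairing low with low and high with high, that the gain is at least 5%. The documents support neither: the assumed ranges also contain 0.3 against 0.3, where the gain is nil.

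**Replacing weight could do harm.** This also stands. A reader might infer that 1-week BMI z should take the place of weight. A swap helps only if BMI z predicts better. Adding it avoids the risk in large samples.

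**The plan already permits further covariates.** It does, so nothing forbids the addition. But that clause does not name 1-week BMI z, and a covariate chosen for the primary test once data are in hand is a discretionary choice. What is missing is prespecification.

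**Infant weight may be shorthand.** Section 1 groups BMI z, weight-for-length z and weight-for-age z as weight outcomes, so the baseline term might be meant loosely. The wording is not conclusive; if BMI z is meant, the same sentence should say so.

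**The 1-week measures may follow allocation.** Randomisation is listed first at Home Visit 1. The planned 1-week weight has the same timing, and the programme sessions start at 3 weeks, so BMI z is no worse placed as a baseline.

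**The trial has power to spare.** At d = 0.4 with about 157 per arm, unadjusted power is about 94%. But the 0.4 in section 7b comes from night sleep and conditional weight gain, not from BMI z. The objection limits the importance of the point without removing it.

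**Conclusion.** The point holds as a free improvement. The primary model omits an already collected baseline value of its own outcome, and no section names that value as a covariate.

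This concerns efficiency and chance imbalance, not bias. A reader might infer that the planned comparison is invalid; it is not, because randomisation protects it under either covariate and the plan already adjusts for one baseline growth measure.

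The size is unknown and may be close to zero. Under the assumed correlations, BMI z in place of weight leaves 0% to 22% less residual variance, and adding it to weight gives about 8% less in the worked example. Detectable d at 157.5 completers per arm is 0.317 unadjusted, 0.302 to 0.310 with weight, and 0.274 to 0.302 with BMI z. The firm part is the direction: with weight kept, adding BMI z does not raise the variance in large samples. No conclusion of the trial is shown to be at risk.

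**What to change.** In section 7a, Specific Aim 1, extend the sentence that defines the 16-week model. Prespecify, as an added covariate, the 1-week value of the same index as the outcome: 1-week BMI z for the primary analysis and 1-week weight-for-length z for that outcome. The same rule can cover weight-for-age z, where little gain is expected. Keep 1-week weight adjusted for gestational age in every model, so that the change is an addition and not a replacement. Make the same addition to the infant covariates in section 6, Demographics and Health.

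The cost is a sentence of wording and one degree of freedom in the model. No new measurement, visit or data item is needed. The change should be fixed before the outcome data are examined by arm.
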